### Phase 2: implementation of interventions

Both CAE and eTAU are brief adjuncts to standard mental health treatment, and trial participants will continue to receive treatment with their regular mental health clinicians. Both arms will have remotely administered pill monitoring via an automated device called an eCAP^TM^ that records pill bottle openings to a secure, cloud-based database. CAE interventionists will be licensed social workers or mental health clinicians with equivalent training supervised by a PhD-level psychologist. A treatment manual for CAE has been developed which is intended for use by mental health staff in public-sector settings such as social workers and counselors. The manual provides explicit guidelines regarding how modules should be co-administered in single or multiple sessions to minimize redundancy and burden. The manual will be modified based on feedback from the SAB prior to implementation. Adapted content will include an optional modular content “toolkit” that will be appropriate for application in diverse settings and with diverse patients. An example of a toolkit item might be resources for helping individuals manage adherence with non-psychotropic medication prescribed for comorbid health conditions common among individuals with BD.

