### Fidelity

Training of interventionists and measures to ensure fidelity to CAE will be similar to the procedures used in the CAE efficacy RCT for content/format for the duration of the study. To ensure generalizability of results to public-sector settings, each interventionist will devote only a portion of their overall time (0.25FTE) to the CAE intervention. After the initial training and throughout the study, CAE sessions will be recorded and 25% of the sessions (approximately 4 sessions every month) will be randomly selected and reviewed for fidelity by the senior interventionist or a fidelity rater trained by the senior interventionist. Fidelity assessment during the course of the study will evaluate CAE module-specific tasks on a Y/N or 0–10 scale. MET module fidelity assessment will include elements of the Motivational Interviewing Treatment Integrity (MITI) code [60]. Finally, CAE interventionists will participate in periodic teleconferences run by the senior interventionist to discuss implementation issues that may arise over time and in order to maintain standard approaches and minimize any potential variability.

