### Data analysis plan

For the primary intent-to-treat analyses (Aim 2), mixed effects longitudinal analysis of TRQ past week and past month over the 6 time periods will be conducted. The intention-to-treat sample will include all enrolled participants who complete baseline evaluation. A treatment variable will be included to indicate randomization to either CAE or eTAU. The lead trial statistician will be blinded for the analysis. Within the longitudinal model, significant interaction of the treatment variable with time indicates that the treatments have a different course of response. We will first fit models with time as a continuous covariate. Alternatively, we will also consider time period as a categorical variable. These interactions will be of primary interest. To account for possible imbalances across treatment groups and other sources of variation, explanatory variables such as sex and ethnicity and BD diagnosis type (I vs. II) will be considered for inclusion in the mixed models. Random effects will include a random intercept and possibly a random slope or other function of time as needed to suitably capture the within-person correlation structure. For TRQ, high success rates may lead to values concentrating on or close to the value zero in terms of percent medication missed, but there may be some persistent non-adherence as well, leading to non-normal data. With prior study data, we have taken the difference in subsequent TRQ scores from the baseline TRQ score to obtain resultant data that appear normally distributed. This is the approach we adopt for the power analysis below. As appropriate, we will also consider representing scores as binary outcomes, indicating whether or not an adherence threshold has been met (e.g., 80% adherent). We will thus consider generalized linear mixed models for binary outcomes (SAS PROC GLIMMIX), as well as fitting a longitudinal model on the difference values with baseline value adjustment. Graphical methods will be used extensively to examine distributions of residuals, identify potentially influential points, and guide data transformations to better approximate normality if warranted. Sensitivity analysis of results will be conducted by modeling a range of plausible correlation structures. Importantly, we will systematically assess the missing at random (MAR) assumption for mixed models. We will assess the sensitivity of the results through pattern mixture and selection model approaches that relax the missing at random assumptions [84].

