### Power analysis

Sample size projections are based on computations from the Repeated Measures and Sample Size (RMASS) software [90] with inputs estimated from prior study data. For sample size requirement for Aim 2, we used past-week TRQ as an approximation of expected and longer-term maintenance adherence status, and we consider primary outcomes to be at 6 months. First, note that at 6-month follow-up, there was a 34.6% improvement in TRQ observed with the CAE pilot, compared to 25.5% in the prior control arm (EDU). The control comparator used in the effectiveness trial, eTAU, is less intensive, with no extra face-to-face sessions, in contrast with EDU. For the control arm in a previous BD RCT [91], a 7% improvement in self-reported adherence was reported. The average of these differences is around 18%. Also, to alleviate deviation from normality, we model difference values from baseline, adjusting for the baseline value as a covariate. We note that compound symmetry and autoregressive (AR(1)) covariance models led to similar model fits in terms of treatment effect *p*-values and model fit criteria. Finally, in the previous CAE R01 study, we observed approximately 20% attrition by 6 months. We thus believe it is conservative to assume the following: (1) There is a mean difference of 16% in improvement from baseline at 6 months between CAE and eTAU; (2) under an error correlation structure of compound symmetry, suppose a small within-subject correlation near 0.08 and an error variance of 504, as estimated value from the data; and (3) assume that attrition will be 30% by 6 months. For a two-sided test of the treatment by time interaction effect being equal to zero, with alpha = 0.025 and power = 0.80, the required total sample size is approximately 182 in total.

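### CAE is delivered by individual interventionists and eTAU by none, but the model and sample size allow only for within-person correlation, so alpha 0.025 and power 0.80 are conditional on no interventionist variance

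*Protocol article*

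**What the plan says.** Individuals are randomised 1:1, 95 per arm. On delivery of CAE, the section Phase 2: implementation of interventions states: "CAE interventionists will be licensed social workers or mental health clinicians with equivalent training supervised by a PhD-level psychologist". The CAE section describes about five sessions per participant and one check-in call with the interventionist. The Fidelity section adds that "each interventionist will devote only a portion of their overall time (0.25FTE) to the CAE intervention", and gives generalisability to public-sector settings as the reason. It lists training, review of a quarter of sessions and periodic teleconferences as ways to keep delivery uniform. The eTAU section describes a pill cap and automated texts, with no interventionist.

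For the analysis of TRQ, the Data analysis plan names "a random intercept and possibly a random slope or other function of time as needed to suitably capture the within-person correlation structure". GAF is to be analysed in a similar way. For TRQ, the Power analysis asks the reader to "suppose a small within-subject correlation near 0.08 and an error variance of 504"; for GAF it uses a compound-symmetry correlation of 0.04. Neither section has a term for the interventionist.

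**The concern.** CAE participants who share an interventionist may have correlated outcomes, and eTAU participants have no such grouping. This is a partially nested design even though individuals are randomised. A person-level intercept or slope cannot absorb correlation between different people treated by the same interventionist.

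Interventionists act only after baseline, so differences between them show up as differences in change, which is what the treatment-by-time test examines. Because the part-time staffing is justified by generalisability, readers will probably take the result to apply to CAE delivered by other community staff. For that conclusion, variation between interventionists is part of the uncertainty. Leaving it out makes the intervals for both alpha-controlled outcomes too narrow and the stated power too high.

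**Working it through.** **Inputs from the Power analysis.** The test: "For a two-sided test of the treatment by time interaction effect being equal to zero". The effect: "There is a mean difference of 16% in improvement from baseline at 6 months between CAE and eTAU". The variance: 504, with within-subject correlation 0.08. Attrition: "assume that attrition will be 30% by 6 months". The result: "with alpha = 0.025 and power = 0.80, the required total sample size is approximately 182 in total". The recruitment target is 190.

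**Step 1: the plan's own figure.** Take a linear-trend contrast c over the four assessments up to 6 months, treated as equally spaced: c = (-1.5, -0.5, 0.5, 1.5).
- c'Sc = 5 x 504 x (1 - 0.08) = 2318.4
- c'mu = 16 x 5/3 = 26.67
- N = 4 x (2.241 + 0.842)^2 x 2318.4 / 26.67^2 = 124
- Allowing for attrition: 124 / 0.70 = 177

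This is within 3% of 182. The article does not state the number and spacing of time points or the attrition pattern, and other choices give other values. The figure of 182 is therefore plausible and is not disputed. No interventionist term is needed to reach it. The GAF figure of 180 is taken as stated.

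**Step 2: power without clustering at 190.** Calibrate so that 182 gives 0.80. The standardised effect is (2.241 + 0.842) x sqrt(190/182) = 3.150, and power = P(Z > 2.241 - 3.150) = 0.818.

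**Step 3: add interventionists. Assumptions, not in the documents:**
- k interventionists with equal caseloads, and each participant stays with one of them.
- 95 x 0.70 = 66.5 CAE participants remain at 6 months, so m = 66.5/k.
- ICC is the interventionist share of the variance of the tested contrast, and all of it enters that contrast.

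Formulas:
- CAE design effect: DE = 1 + (m - 1) x ICC; for eTAU it is 1.
- True over planned standard error: s = sqrt((DE + 1)/2).
- Actual alpha of the planned test: 2 x P(Z > 2.241/s).
- Power of a test with the correct standard error: P(Z > 2.241 - 3.150/s).

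Example, k = 4 and ICC 0.05: m = 16.6; DE = 1.78; s = sqrt(2.78/2) = 1.18; alpha = 0.057; power = 0.67.

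| k | ICC | s | Actual alpha | Power at 190 |
|---|---|---|---|---|
| any | 0 | 1.00 | 0.025 | 0.82 |
| 8 | 0.01 | 1.02 | 0.028 | 0.80 |
| 8 | 0.05 | 1.09 | 0.039 | 0.74 |
| 4 | 0.01 | 1.04 | 0.031 | 0.79 |
| 4 | 0.02 | 1.08 | 0.037 | 0.75 |
| 4 | 0.05 | 1.18 | 0.057 | 0.67 |
| 2 | 0.05 | 1.34 | 0.095 | 0.54 |

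A simulation of the 6-month change contrast under no average effect (20,000 runs, variance 504, 66 per arm) agrees on alpha at ICC 0.05: 0.054 for k = 4 and 0.093 for k = 2.

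The alpha column depends only on k, the ICC and retention, so it applies to GAF under the same assumptions.

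**Step 4: is a small k plausible?** Fidelity review of a quarter of sessions at about 4 a month implies 4/0.25 = 16 sessions a month. A few staff at 0.25 FTE could cover that. This is an inference, since the article gives no number.

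**Step 5: cost of estimating the variance.** With Satterthwaite degrees of freedom for few interventionists, power at k = 4 falls further, to 0.61 (ICC 0.02) and 0.49 (ICC 0.05).

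**The case against.** A reader might infer that the standard error is simply wrong and that alpha is certainly above 0.025. The documents do not support that. If CAE has no effect for anyone, interventionists cannot differ in effect, and the planned test keeps its level. It can also be defended for the average effect as delivered by the trial's own interventionists. Inflation needs interventionists who differ and a target that extends beyond them. The Fidelity section points towards generalisation but does not say that interventionists are sampled from a population. This objection stands, and the point is conditional for that reason.

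A reader might also infer that interventionist variation enters the treatment contrast in full. When differences from baseline are modelled, an effect that is constant across post-baseline visits enters the treatment-by-time contrast only in part. The table is then an upper bound on the harm.

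Other points also soften the size:
- The Power analysis calls its inputs conservative: 16 rather than about 18 points, and 30% rather than about 20% attrition. With 18 points and 20% attrition, power at k = 4 is 0.82 (ICC 0.05) or 0.89 (ICC 0.02); at k = 2 and ICC 0.05 it is still 0.69.
- The power column rests on calibration to the plan's 0.80. For a simple comparison of 6-month change at variance 504, power is 0.97 without clustering and 0.89 at k = 4 and ICC 0.05.
- Manualised delivery and session review aim to keep the ICC low.

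Finally, this could be called detail for an analysis plan not shown. The article, however, itself states the random effects, the sizing correlations, alpha and power. Its broad references to other sources of variation and alternative correlation structures name no interventionist effect.

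**Conclusion.** The point holds in conditional form. The partially nested structure is clear from the article, and the stated random effects and sizing correlations stop at the person. If interventionists differ and the conclusion is to extend beyond them, alpha 0.025 and power 0.80 are correct only at zero interventionist variance.

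Under the assumptions in the working, 4 to 8 interventionists and an ICC of 0.01 to 0.05 give alpha of about 0.028 to 0.057 and power of about 0.80 down to 0.67. At the mild end (k = 8, ICC 0.01) the margin of 190 over 182 keeps power at 0.80, though alpha has no such margin. The two inputs that drive the size are unknown, so this is a worthwhile and inexpensive improvement to the plan. It is not a demonstrated error in it.

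**What to change.** 1. Record the delivering interventionist for every CAE participant.
2. For TRQ and GAF, prespecify a partially nested mixed model as a sensitivity analysis. It has interventionist and interventionist-by-time random effects in the CAE arm only, fitted by REML with small-sample degrees of freedom. Report interventionist-specific CAE estimates beside it.
3. Make that model primary only if there are enough interventionists to estimate the variance. Otherwise keep the planned model as primary and word the conclusion as conditional on these interventionists.
4. In the Power analysis, state that 0.80 assumes no interventionist variance, and give power for both outcomes over an ICC range such as 0 to 0.05 at the actual number of interventionists.

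The cost is one identifier, a few lines of text and a restated power, with no extra participants or staff. The downside is a wider interval in the nested analysis and a less favourable stated power.

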### Power analysis

Sample size projections are based on computations from the Repeated Measures and Sample Size (RMASS) software [90] with inputs estimated from prior study data. For sample size requirement for Aim 2, we used past-week TRQ as an approximation of expected and longer-term maintenance adherence status, and we consider primary outcomes to be at 6 months. First, note that at 6-month follow-up, there was a 34.6% improvement in TRQ observed with the CAE pilot, compared to 25.5% in the prior control arm (EDU). The control comparator used in the effectiveness trial, eTAU, is less intensive, with no extra face-to-face sessions, in contrast with EDU. For the control arm in a previous BD RCT [91], a 7% improvement in self-reported adherence was reported. The average of these differences is around 18%. Also, to alleviate deviation from normality, we model difference values from baseline, adjusting for the baseline value as a covariate. We note that compound symmetry and autoregressive (AR(1)) covariance models led to similar model fits in terms of treatment effect *p*-values and model fit criteria. Finally, in the previous CAE R01 study, we observed approximately 20% attrition by 6 months. We thus believe it is conservative to assume the following: (1) There is a mean difference of 16% in improvement from baseline at 6 months between CAE and eTAU; (2) under an error correlation structure of compound symmetry, suppose a small within-subject correlation near 0.08 and an error variance of 504, as estimated value from the data; and (3) assume that attrition will be 30% by 6 months. For a two-sided test of the treatment by time interaction effect being equal to zero, with alpha = 0.025 and power = 0.80, the required total sample size is approximately 182 in total.

Sample size requirement analyses were also conducted for GAF, the outcome measure for Aim 3. Again, inputs are based on estimates from the prior CAE R01 study. The observed mean increase in the CAE arm over 6 months was 6.1, and the difference between CAE and EDU was 3.5. In other BD RCTs conducted by this study team [91], little to no difference was observed from controls in GAF. As noted above, eTAU will be less intensive. Thus, we assume (1) a mean difference value of 4.8; (2) error variance of 48.3 with compound symmetry correlation of 0.04; and (3) 30% attrition at 6 months. For two-sided Type I error of 0.025, we estimate that 180 subjects will achieve power = 0.80. Thus, overall, for simultaneous Type I error between tests for Aims 1 and 2 to be at most 0.05, for power = 0.80 for each test, and to allow for some deviation from the assumptions used in the above power calculations, we will recruit a total of 190 subjects.

### Qualitative data analysis

In qualitative research, data collection, coding, and analysis occur simultaneously rather than sequentially. Emerging insights can be incorporated into later stages of data generation, enhancing the comprehensiveness of the results [92]. Transcript-based analysis [93, 94] will be used to analyze all qualitative data. In this method, the researcher uses the transcription itself as the source of the textural data to be analyzed. We will use a thematic content analysis approach to data analysis, encompassing open, axial and sequential coding, and the constant comparative method to generate constructs (themes) and elaborate the relationship among constructs [93, 94]. A coding dictionary that includes mutually exclusive code definitions will then be constructed. The coding structure will be reviewed after a preliminary analysis of a sub-sample of transcripts, and the dictionary will be refined through comparison, categorization, and discussion of each code’s properties and dimensions [93, 95].

### Provisions to monitor the data to ensure the safety of research participants

The data and safety monitoring plan for this project consists of three components, as outlined below.

#### Component 1

Approval from the local IRB will be obtained prior to performing any research related to this study, and approval will be maintained throughout the study period via continuing review.

#### Component 2

The project principal investigators (PIs) will review safety on an ongoing basis. The PI will meet regularly with staff (weekly or as necessary) to review any and all adverse events and to review the study data collected since the previous meeting. In addition, there are several committees within the larger study team that are involved in oversight of trial conduct and monitoring. These include the Study Coordinating Committee which is co-chaired by the study PIs, project manager, and research coordinators. The Study Coordinating Committee will be convened prior to the initiation of the project and will meet at regular intervals throughout the project. Meetings will be held in person or via videoconference. Additional meetings may be scheduled as necessary. Minutes of all meetings will be kept for reference and distributed to other relevant members of the study team as appropriate. A Clinical Trial Coordination Subcommittee will oversee patient recruitment, enrollment, assignment to treatment arm, scheduling of assessments, and patient flow through the trial. This subcommittee is chaired by study PIs, who will supervise the research assistant devoted to recruiting and patient enrollment. The Data Management Subcommittee is tasked with ensuring accurate data collection related to patient recruiting, enrollment, assessments, and interventions. This committee is chaired by the senior statistician lead who supervises the data management staff. The Data Management Subcommittee will ensure data integrity, completeness, and accuracy will be verified on an ongoing basis by this committee.

#### Component 3

The Data Safety and Monitoring Board (DSMB) will be comprised of a faculty member in the School of Medicine Department of Psychiatry who has expertise in BD, a faculty member who has expertise in the delivery of care in community mental health clinic settings, and a biostatistician. None of the DSMB will be part of the study team or affiliated with the trial sponsor, but all will have extensive experience with federally funded research and/or behavioral interventions. The DSMB will provide oversight of the proposed study via regular reports submitted to the DSMB by the PIs (minimally on an annual basis), telephone or email communication for issues that need more immediate attention, and ad hoc face-to-face meetings that might be called to evaluate unanticipated serious adverse events.

For this no-more-than-minimal risk behavioral study, adverse event reporting will be based on spontaneous reporting from study participants. Adverse events will be identified by the study investigators and/or qualified research assistants. All adverse events, whether considered serious or not, will be recorded and reviewed by the study PI on an ongoing basis, and reported to the IRB according to local IRB policy. Serious adverse events are defined as events that result in any of the following: death; a life-threatening experience; inpatient hospitalization or prolongation of existing hospitalization; a persistent or significant disability/incapacity; or a congenital anomaly/birth defect (or an event that may require medical or surgical intervention to prevent one of the outcomes listed above). Given that this is deemed a minimal risk trial, there will be no interim analyses or stopping guidelines.

All participants will continue with their psychiatric providers during and following the trial. Any participant at risk for imminent harm to self or others will be handled on a case-by-case basis. Participants will be terminated from the trial if deemed unsafe to continue in study procedures by the PI or the participant’s clinician (such as for worsening condition or increased harm risk), if the participant requests to be removed or withdraws consent, or if the participant is lost to follow-up. Since the intervention is an addition to their regular treatment and does not include medication, there will be no follow-up with the research team. Should the need arise to discontinue a patient from the study because of symptom worsening or for any other reason, we will collaborate with their non-study-related clinician to determine treatment options for that patient following study discontinuation. There will be no post-trial care or compensation for those who suffer harm from trial participation.

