## Introduction

### Background and rationale

A cornerstone of treatment uniformly recommended by guidelines on treatment for individuals with bipolar disorder (BD) [1] is mood-stabilizing medication such as lithium, anticonvulsants, or second-generation antipsychotic drugs [2–5]. However, approximately 50% of individuals with BD are poorly adherent with their medication [6–9] often leading to severe and negative consequences [10–16]. Poor adherence in BD is associated with poor recovery and high relapse [17]. Gonzalez-Pinto [18] reported a 5.2-fold increased suicide rate in BD patients with poor adherence compared to adherent BD patients [18]. Other reports note substantially increased costs for individuals with poor vs. good adherence [19, 20]. Since poor adherence in BD is a robust predictor of mood relapse [21], adherence promotion is a logical target for BD treatment and recovery efforts.

A review on BD adherence research studies conducted by this study team suggests that while a variety of approaches including psychoeducation, motivational interviewing, financial incentives, and cognitive behavioral treatment can all be of some benefit in improving medication adherence in BD, there is no single approach that appears to have superior adherence promotion efficacy, and there are very limited data on how adherence enhancement approaches can be implemented in clinical settings where most people with BD receive care [1]. Two literature reviews on the topic of BD adherence highlighted the fact that interventional approaches need to be flexible and designed to adapt to different settings and patients [22, 23].

The COVID-19 global pandemic has underscored the need to have interventions that are amenable to virtual delivery [24]. However, a recent systematic literature review by Basit and colleagues on telemedicine interventions for pharmacological adherence in persons with bipolar disorder, schizophrenia, or major depressive disorder [25] found only a limited number of trials (*N*=17) and only two studies that included individuals with BD. Another recent review on eHealth interventions in individuals with chronic health conditions generally found that a majority of interactive eHealth interventions are effective in improving adherence to long-term medication [26]. Intervention strategies that improve patient’s treatment involvement and their medication management skills appear most promising [26].

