In Phase 2 (months 7–60), we will conduct a prospective, randomized effectiveness-implementation superiority trial of technology-facilitated CAE vs. enhanced treatment as usual (eTAU). In total, 190 participants will be randomized at baseline on a 1:1 basis to receive either CAE (*N* = 95) or eTAU (*N*=95). CAE is a brief adjunct to standard mental health care. The primary outcome is adherence measured by the Tablet Routines Questionnaire (TRQ) and validated with electronic pill monitoring via eCAP^TM^. Secondary outcomes include functioning, health resource use, and BD symptoms. All study participants will be followed for a 12-month period. We will assess barriers and facilitators to CAE implementation using both qualitative and quantitative methods. To evaluate patient-level mechanistic targets, we will explore the effects of personal adherence barriers (insufficient or inaccurate BD knowledge, unstable routines, poor treatment alliance, and substance use) and adherence facilitators (care engagement, patient satisfaction, ease of access). Finally, we will assess reach and adoption of CAE among clinicians (referral counts) and health resource use including outpatient care, emergency room visits, and hospitalizations.

In considering the appropriate comparator to CAE in this effectiveness trial, we chose an approach that is generalizable to standard clinical care. Outcome assessment in most adherence trials typically involve monitoring of pill-taking behavior, and it has been noted in previous studies, including this study team’s preliminary work, that adherence monitoring itself is likely to improve adherence [32]. Thus, adding adherence monitoring via electronic pill caps (eCAPs^TM^) and text messaging to standard care is an appropriate and generalizable comparator.

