**Table 2 Tab2:**
[figure not shown]
Phase 2 measures and schedule of events [62]

^a^Service Engagement Scale and Ease of Access question will only be administered at V1

^b^only BPRS and MADRS will be administered at Screen

^c^Baseline should ideally be completed 2 weeks after screen, but no less than 1 week after screen to allow for sufficient time for eCAPs to be used

^d^Individuals who terminate study prematurely will have termination visit study assessments done at the time point that termination actually occurs

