
We will study reasons for dropout and identify variables for possible inclusion in binary regression models of dropout by 10 weeks. Treatment differences in dropout models will be of interest. Additionally, we will compare corresponding TRQ and eCAP^TM^ adherence levels. Correlation between the measures will be estimated and Bland-Altman plots will be generated [85]. Secondary follow-up analyses at 9 and 12 months will also be compared in longitudinal analyses.

For Aim 3 and additional secondary analyses, GAF scores will be analyzed in a similar manner as in Aim 2. From previous experience, we expect GAF scores to approximately be normally distributed. Exploratory analysis will examine whether reductions in adherence barriers (e.g., BD knowledge, medication routines, communication, and substance) and increases in facilitators (patient satisfaction, ease of access, engagement) mediate the treatment effects on adherence. Further, secondary analyses will assess the mediation effects on functioning through adherence improvement. We will conduct simple mediation analyses, as well as multiple mediator models, using approaches described by Mackinnon and colleagues [86] and Preacher and Hayes [87]. Potential confounder variables will be included as covariates, such as age, sex, ethnicity, health literacy, BD type I vs. II, and substance use comorbidity. Bootstrapping methods will be used to assess indirect effects [87]. We will also consider, as needed, use of generalized linear models through a mediation formula approach [88, 89] to estimate the direct effect of the treatment and indirect effects through each mediator as well as through the set of mediators. Variable selection methods such as lasso will be used when multiple mediators are considered simultaneously to reduce redundancy. Moderators of treatment to be explored for each of the primary outcome models include covariates such as age, sex, ethnicity, health literacy, BD type I vs. II, and substance use comorbidity.

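### Participants terminated for worsening or harm risk have no outcome assessment after the termination visit, although the plan promises 12 months of follow-up for everyone

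*Protocol article*

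**What the plan says.** All statements are in the protocol article.

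- Trial design: "All study participants will be followed for a 12-month period".
- Assessments and outcomes: visits at screening, baseline, 10 weeks, 6, 9 and 12 months.
- Provisions to monitor the data to ensure the safety of research participants: a participant is terminated if the PI or the participant's clinician judges it unsafe to go on ("such as for worsening condition or increased harm risk"), on withdrawal of consent, or when lost to follow-up. The next sentence, which gives as its reason that the intervention is an add-on without medication, says "there will be no follow-up with the research team".
- Table 2, note d: "Individuals who terminate study prematurely will have termination visit study assessments done at the time point that termination actually occurs". No assessment after that visit is described.
- Data analysis plan: "The intention-to-treat sample will include all enrolled participants who complete baseline evaluation". On missing data: "We will assess the sensitivity of the results through pattern mixture and selection model approaches that relax the missing at random assumptions". On dropout: "We will study reasons for dropout and identify variables for possible inclusion in binary regression models of dropout by 10 weeks".

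**The concern.** The plan does not separate stopping study sessions from leaving data collection. A person taken out because their condition worsened contributes one assessment at that moment and then nothing, while still counting in the intention-to-treat sample.

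The reason for the loss bears on what the trial measures. GAF is the Aim 3 outcome, with its own sample-size calculation at a two-sided 0.025. The symptom scales record worsening directly. Emergency visits and hospitalisations would go unrecorded in people who may be likely to have them.

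The arms could also differ in how often this happens. CAE adds about six staff contacts that eTAU lacks (four core sessions, a booster and a check-in), and neither participants nor assessors are blinded. If loss differs by arm and the unseen outcomes are worse than the model expects, the treatment contrast is biased.

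**Working it through.** **1. What is lost.** Someone terminated between 10 weeks and 6 months misses three scheduled assessments (6, 9 and 12 months), including the 6-month one that the Power analysis treats as primary. Someone terminated between baseline and 10 weeks misses four. In each case one unscheduled termination visit is gained.

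**2. What the attrition allowance does.** The Power analysis gives a TRQ difference of 16, error variance 504, within-subject correlation 0.08, 30% attrition by 6 months, two-sided alpha 0.025 and power 0.80, and states about 182 in total. Take the change from first to last time point, with retention r at the last one:

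n per arm = (z₀.₉₈₇₅ + z₀.₈₀)² × 2σ²(1 + 1/r − 2ρ) / Δ²

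- Reading 504 as residual variance, σ² = 504/0.92 = 547.8. With r = 0.70: 9.505 × 2 × 547.8 × 2.2686 / 256 = 92.3, so 93 per arm and 186 in total, 2.2% above 182.
- Reading 504 as total variance gives 170. The article does not state the number of time points, so the match depends on the reading, and no error is claimed.
- With r = 1 on the first reading: 9.505 × 2 × 547.8 × 1.84 / 256 = 74.9, so 75 per arm and 150 in total.

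Retention enters only through the variance. The allowance therefore protects power and does nothing about bias. Of 190 randomised, 30% is 57 people and the 20% seen in the earlier study is 38. The article does not say how many of these would be terminations for worsening rather than withdrawn consent or lost contact.

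**3. What a bias would look like.** Let q be the share of an arm terminated for worsening. Let D be how much worse their unseen outcomes are than the model predicts from the data already seen, including the termination visit.

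Bias in the arm contrast = q(CAE) × D(CAE) − q(eTAU) × D(eTAU)

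With the same D in both arms, this is the difference in q times D. No value of q or D stands in the document; those below are assumptions that show scale only.

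| Outcome | Arm difference in q | D | Bias | Share of planned effect |
|---|---|---|---|---|
| GAF | 0.05 | 10 | 0.5 | 10% of 4.8 |
| GAF | 0.10 | 10 | 1.0 | 21% of 4.8 |
| GAF | 0.10 | 15 | 1.5 | 31% of 4.8 |
| TRQ | 0.03 | 10 | 0.3 | 2% of 16 |
| TRQ | 0.10 | 30 | 3.0 | 19% of 16 |
| Either | 0 | any, equal | 0 | 0% |

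More such terminations in CAE would flatter CAE; more in eTAU would do the reverse. D shrinks toward zero as far as the termination visit captures the worsening.

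**4. Which outcomes are exposed.** For GAF, symptoms and service use the link to worsening is direct. For the TRQ it is inferred. The Background supports it ("Since poor adherence in BD is a robust predictor of mood relapse"), but the BD symptoms section calls the relation between symptoms and adherence inconsistent.

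**The case against.** **The sentence may concern care, not measurement.** Its stated reason is about treatment, and the text around it deals with clinical arrangements, so it could mean no clinical follow-up by the team. This ambiguity is real. On either reading, though, the termination visit is the last assessment described, and the Trial design statement still does not fit.

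**The termination visit helps.** It falls at the event. If it records the worsening and dropout depends on that record, the data are missing at random and the planned mixed model can use them. This stands. A reader might infer that the data are missing not at random by design; the document does not support that. What remains is doubt: the decision rests on judged risk that the scales may not fully capture.

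**The analysis plan already responds.** It will assess the missing-at-random assumption, run pattern-mixture and selection models, and study dropout reasons and arm differences. This is sound practice, but it explores assumptions about values that were not collected. The dropout models also stop at 10 weeks, before the 6-month primary time point.

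**Differential loss is speculative.** Termination is decided by the PI or the participant's own clinician, and both arms keep their regular clinicians. A reader might infer a bias in favour of CAE; neither its direction nor its presence can be established.

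**Recovery will be partial.** Assessments are themselves study procedures, so the judgement that ends participation may also rule out contact. A reader might infer that most of the lost data could be had, or that records would supply service use. The first is unsupported, and record checks cover only a random 20% subset.

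**This is a condensed article.** The full protocol may separate the two kinds of stopping. But the point rests on statements the article makes that do not fit together, not on silence.

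**Conclusion.** The point holds as an inconsistency with an avoidable cost in data. The article promises 12 months of follow-up for all and counts everyone with a baseline, yet describes no outcome collection after termination. The intention-to-treat definition is not itself breached, since it fixes who is counted; what is missing is their later outcomes. The loss is plausibly informative for GAF, symptoms and service use, and less certainly for the TRQ.

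The size and direction of any bias cannot be derived from the document. Under the assumed ranges above it is 0.5 to 1.5 GAF points or 0.3 to 3.0 TRQ points, smaller where the termination visit carries the information, and zero where loss and gap are equal in the arms. No stated sample size changes. This is an inexpensive improvement worth making, not a flaw that invalidates the design.

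**What to change.** Reconcile the Trial design section, note d to Table 2 and the safety section by stating that the end of study sessions is not the end of outcome collection. Leave the termination criteria as they are.

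Unless consent for data is withdrawn, or the PI or clinician judges contact unsuitable, collect the remaining scheduled TRQ, GAF and self-reported service-use items remotely. The Study setting section already allows video, phone and REDCap survey, and eCAP data can be uploaded remotely. Analyse these values in the assigned arm, and enter the termination visit at its actual date.

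The cost is protocol and consent wording and a small number of extra remote assessments. Some terminated participants will still not be recoverable, so the planned sensitivity analyses remain necessary.
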